### Outcomes

The efficacy of the surgical method will be defined as the lack of surgical wound complications (infection, hematoma, hernia as late complication of wound infection…) and reduced severe complications. The primary composite endpoint will comprise two measures of success: Having either a surgical wound infection or a Clavien IIIb-IV postoperative complication constitute the primary composite endpoint. This means, that a patient having either a surgical wound infection or a Clavien IIIb-IV [10] complication would be scored as a “1”. Surgical wound infection will be assessed at the 30 postoperative day visit using specific wound assessment questions (purulent drainage, positive wound cultures, wound opened to drain and classical flogotic signs). These questions are recorded at the eCRF (Yes recorded as 1, No recorded as 0). In all cohorts, secondary endpoints will include oncologic results at 2 years, overall survival, disease-free survival, local recurrence, metastases rate, rate of unplanned conversions to open surgery, operative time (min), complete mesocolic excision, number of harvested lymph nodes, R0 resection, length of stay (days), ventral hernia (assessed 1 and 2 years after the right colectomy), patient-assessed quality of life measures (the European Organization for Research and Treatment of Cancer Quality of Life Questionnaires C30 and CR29), and systemic inflammatory response syndrome (C-reactive protein, with optional procalcitonin). Optional measures, to enable a medico-economic sub-study, include EQ-5D, time to ambulation, patient return to work/activity, pain evaluation, and resource utilization for procedure and follow-up care.

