**Methods/design:**

MIRCAST is the Minimally-Invasive Right Colectomy Anastomosis Study that will compare laparoscopy with robot-assisted surgery, using either intracorporeal or extracorporeal anastomosis, in a large prospective, observational, multicenter, parallel, four-cohort study in patients with a benign or malignant, non-metastatic tumor of the right colon. Over 2 years of follow-up, the study will prospectively evaluate peri- and postoperative complications, postoperative recovery, hospital stay, and mid-term results including survival, local recurrence, metastases rate, and conversion rate. The primary composite endpoint will be the efficacy of the surgical method regarding surgical wound infections and postoperative complications (Clavien-Dindo grade III-IV complications at 30 days post-surgery). Secondary endpoints include long-term oncologic results, conversion rate, operative time, length of stay, and quality of life.

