## Methods/design

### Patient recruitment

Patients included in the study will be adults (male or female aged ≥18 years) with a benign or malignant tumor in the right colon that require an elective right colectomy with curative intent. Patients will have a life expectancy of at least 12 weeks, with an adequate performance status (Eastern Cooperative Oncology Group Scale score ≤ 2). All patients will have voluntarily signed and dated an Ethics Committee-approved informed consent form before inclusion, obtained by the investigator or designee. Patients will be excluded if they have cT4b tumors, metastatic disease, planned colonic surgery along with other major concomitant procedures (e.g. liver resections, other intestinal resections), or have inflammatory bowel disease (i.e. Crohn’s disease or ulcerative colitis). Patients who are pregnant or suspected to be pregnant, have a comorbid illness or condition that would preclude the use of surgery, are undergoing emergency procedures, or are unwilling to comply with all follow-up study requirements will also be excluded. All patients will be screened and recorded during enrolment to identify any selection bias, which can be higher in observational studies [6].

Eligible patients will be recruited from the approved participating centers according to the surgeons’ experience with each technique. It is calculated that at least 1200 patients (300 per cohort) should be enrolled in the study. The assumptions for the sample size were based on the incidence of surgical wound infection and Clavien-Dindo grade > IIIa complications. The sample size is based on attaining a success rate of 85% for the primary endpoint, with the lower 95% confidence limit being no greater than 5% from the estimated success rate. Assuming a 2-sided interval, a total of 245–317 patients will be required within each cohort. Accounting for a 10% loss to follow-up, a total of 1200 patients will be recruited so that the four parallel cohorts will have sufficient power to make multiple comparisons.

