### Data collection and management

Data will be collected prospectively according to the schedules outlined in Fig. 2 and Table 1. Enrolled patients will undergo assessments at the following intervals: preoperatively, intraoperatively through to discharge, 30 days, 90 days, 1 and 2 years post-procedure. At baseline and once patient consent has been obtained, patient demographics and medical history (including indication and planned procedure) will be collected. Patient-related quality of life and functional measures will be completed by the patient. Data related to the operative procedure itself will be collected, including procedure timing, personnel, resource utilization, system and instrument use, need for conversion, complications and technical observations. During the perioperative period until discharge, data collected will include wound infection, complications, 30-day mortality, length of stay, and tumor characteristics. During follow-up, patient-related functional outcomes and quality of life measures will be completed and any complications or protocol deviations reported, according the standard follow-up procedure for each center.

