Patients with missing data in planned surgical approach will be be excluded from the study. Patients with missing data in any end-point will be excluded from the analyses on that end-point, and patients with missing data in variables included in the propensity score will have their data imputed using multiple imputation procedures.

Three sensitivity analyses will be used for the primary end-points. The analysis will be repeated k times omitting a hospital each time (k = number of participant hospitals). In addition to intention-to-treat analysis, a sensitivity analysis will be conducted excluding patients with conversion. The analysis will be repeated stratifying by tertiles of the propensity score.

Stata/SE software will be used to perform the statistical analysis (versions 14–16 [forthcoming]).

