### Sample size calculation

The assumptions for the sample size of this study have been developed based on the incidence of Surgical Wound Infection, as well as the incidence of Clavien-Dindo grade > III complications as seen in the Introduction. The sample size is based on attaining a success rate of 85% for the primary endpoint, with the lower 95% confidence limit being no greater than 5% from the estimated success rate. Assuming a 2-sided interval, a total of 245–317 subjects will be required within each cohort. Accounting for a 10% loss to follow up, a total of 1200 subjects will be recruited for this study. Several interim analysis are planned through the study in order to build new power analysis and adjust sample size accordingly if needed.

The design of this study envisages four parallel cohorts for which the sample size has been developed for each cohort according to a precision around an expected success rate with enough subject and sufficient power to make multiple comparisons within the appropriate method. Any statistical inferences drawn based on pairwise comparisons will be undertaken in a posteriori statistical analysis using a propensity score to account for confounding covariates.

The primary endpoint for success is defined as a patient meeting the following criteria:
Surgical Wound Infection 5% lower in the ICA group.Grade IIIb-IV Clavien -Dindo complications at 30 days post op 5% lower in the ICA group.

According to the current literature the the following numbers represent Surgical Wound Infection and Severe Complications in intermediate volume centers:

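### The primary composite is capped at Clavien IV and does not count death, so a patient who dies by day 30 with no other recorded event scores as a success or may be dropped; the severity range also varies across the article

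*Protocol article*

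**What the plan says.** The Outcomes section gives the operative definition, "Having either a surgical wound infection or a Clavien IIIb-IV postoperative complication constitute the primary composite endpoint", and the scoring rule: "a patient having either a surgical wound infection or a Clavien IIIb-IV [10] complication would be scored as a" 1. Everyone else is left at 0. The success criterion under Sample size calculation and the literature table that follows it use the same IIIb-IV range.

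Three other passages describe the severity range differently:

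- Abstract, Methods/design: "Clavien-Dindo grade III-IV complications at 30 days post-surgery".
- Patient recruitment, as the basis of the sample size: "Clavien-Dindo grade > IIIa complications".
- Sample size calculation, again as the basis: "Clavien-Dindo grade > III complications as seen in the Introduction".

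On death and missing data, the Data collection and management section says of the period up to discharge that "data collected will include wound infection, complications, 30-day mortality, length of stay, and tumor characteristics". The Outcomes section places the assessment of surgical wound infection at the 30-day visit. The Statistical analysis section states: "Patients with missing data in any end-point will be excluded from the analyses on that end-point". It makes no exception for patients who have died.

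**The concern.** The composite is meant to capture failure of the surgical method, and the Outcomes section ties efficacy partly to fewer severe complications. An early death is the most severe result a patient can have. Under the stated scoring rule it produces a 1 only if a wound infection or a IIIb-IV complication was also recorded. Otherwise the death counts in the technique's favour or leaves the denominator.

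This does not depend on how the Clavien-Dindo scale labels death. No statement of the composite names death, every endpoint statement stops at IV, and no rule gives a death a score.

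Two things are at stake. First, the success rate of each cohort is overstated by the share of such deaths, and that rate also drives the interim rule that removes a cohort's data below 75% success. Second, with several severity ranges in print, a reader cannot be sure that the 85% planning rate and the analysed endpoint describe the same events.

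**Working it through.** **Severity ranges side by side**

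| Place | Range | Role | Literal difference from IIIb-IV |
|---|---|---|---|
| Outcomes; success criterion in Sample size calculation; literature table | IIIb-IV | Operative endpoint and planning inputs | none |
| Abstract | III-IV | Endpoint | adds IIIa |
| Patient recruitment | > IIIa | Sample-size basis | no upper cap |
| Sample size calculation, opening | > III | Sample-size basis | drops IIIb, no upper cap |

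There are four distinct ranges. Only the Abstract states a different endpoint; the two open-ended forms describe what the sample size was based on.

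**Paths for a patient who dies by day 30**

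1. Wound infection or a IIIb-IV complication recorded before death: scores 1.
2. Neither recorded, composite taken as complete: scores 0, a success.
3. Neither recorded, 30-day wound assessment taken as missing: excluded from the primary analysis.

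The problem is confined to paths 2 and 3.

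**Size**

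The article gives no mortality, so there is no figure of its own to reproduce. Inputs from the article: 300 patients per cohort, 85% success, and an interim look with at least 75 patients per cohort and a 75% limit. Assumptions: 30-day mortality *m* of 0.5% to 2%, and every death on path 2 or 3. The second assumption makes the result an upper bound.

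- Successes and failures per cohort: 300 × 0.85 = 255 and 300 − 255 = 45.
- Deaths per cohort: 300 × 0.005 = 1.5, to 300 × 0.02 = 6.
- Deaths scored 0: 255/300 = 85.0%.
- Deaths dropped: (255 − 1.5)/(300 − 1.5) = 84.9%, to (255 − 6)/(300 − 6) = 84.7%.
- Deaths counted as failures: (255 − 1.5)/300 = 84.5%, to (255 − 6)/300 = 83.0%.
- Relative to the 45 expected failures: 1.5/45 = 3.3%, to 6/45 = 13.3%.

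**Interim rule**

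With 75 patients, one patient is 1/75 = 1.3 percentage points. The limit lies at 75 × 0.75 = 56.25 successes, so 57/75 = 76.0% is kept and 56/75 = 74.7% is excluded. If one of those 57 successes is a death, scoring it 0 gives 76.0% (kept), dropping it gives 56/74 = 75.7% (kept), and counting it as a failure gives 74.7% (excluded). Expected deaths at that size are 75 × 0.005 = 0.4 to 75 × 0.02 = 1.5. A cohort performing at 85% would have about 75 × 0.15 = 11 failures against the 18 that the rule tolerates, so this matters only for a cohort already near the limit.

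**Sample size**

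For a 5-point half-width with the simple normal interval, n = 1.96² × p(1 − p)/0.05². This gives 196 at p = 0.85, 202 at 0.845 and 217 at 0.83. All are below the 300 × 0.9 = 270 evaluable patients left after the stated 10% loss, so adding death does not threaten the planned precision on this calculation.

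**The case against.** The case on the other side has real force on several points.

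- **IIIb-IV dominates.** The operative definition, the success criterion and the planning table agree. Adding the midpoints of the table's two components (ignoring overlap) gives failure of 4.5 + 3.05 = 7.55% for ICA and 12 + 9.5 = 21.5% for ECA. The average is about 14.5%, or about 85.5% success. The derivation of 85% is not stated, but it is compatible with the IIIb-IV endpoint. A reader might infer four competing endpoints; the text does not support that.
- **Known events are safe.** A reader might infer that a patient with a known IIIb-IV event who misses the 30-day wound check is excluded. The scoring rule needs only one of the two components, so that patient already scores 1.
- **Earlier grades are not lost.** A reader might infer that a re-operated patient who later dies is regraded out of the IIIb-IV range. The Complications section has all complications captured and graded, and nothing says that only the final or highest grade counts.
- **An early death need not leave the wound component missing.** Wound infection and complications are also collected up to discharge, so exclusion is a possible reading and not a certainty.
- **The numbers are small.** Setting the deaths against the sparsest component, IIIb-IV events in ICA cohorts at 1.1% (300 × 0.011 = 3.3), could suggest that missed deaths exceed counted events. That pairs the highest assumed mortality with the lowest event rate. The primary endpoint is the composite, and 45 failures is the right comparator. Bias between techniques would also need mortality to differ between them, on which the article offers nothing.
- **The statistical analysis plan is not shown** and may cover deaths and partly missing composites.

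What remains is the scoring rule itself. It is fixed in the protocol article, not left open, and it gives 0 or exclusion for a death with no other recorded event. The Abstract still contradicts the operative definition, and the two sample-size statements still differ from it and from each other.

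**Conclusion.** The point holds in limited form. As written, the primary composite does not count death. A patient who dies by day 30 with no wound infection or IIIb-IV complication recorded beforehand is scored a success, or may be excluded if the wound assessment is treated as missing. The severity range is inconsistent in the Abstract and in both statements of the sample-size basis.

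The effect is modest: at most 0.5 to 2.0 percentage points of success per cohort, or about 3% to 13% of the 45 expected composite failures. This rests on an assumed mortality of 0.5% to 2% and on no dead patient having a prior qualifying event. It could decide the interim exclusion for a cohort of about 75 patients near 75% success, but not for one performing as planned. The reason to act is less the size than that a stated rule for the primary endpoint can count a death as a success, and that correcting it is cheap.

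**What to change.** Use one definition in the Abstract, Patient recruitment, Outcomes and Sample size calculation. Suggested wording: the primary event is a surgical wound infection, a Clavien-Dindo complication of grade IIIb or higher, or death from any cause, by postoperative day 30. Naming death separately removes any reliance on how the scale grades it.

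Add to the missing-data paragraph that a death by day 30 scores 1 and is never treated as a missing endpoint. Confirm that the 85% planning rate refers to this definition, or restate it with the mortality assumed. The literature table can stay as a report of published 3b-4 rates, with a note that deaths are additional if they were not included there.

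Cost: complication grades and 30-day mortality are already collected, so no new data are needed. The reported success rate would be slightly lower. The trial is registered and the primary endpoint changes, so a dated and documented amendment to the endpoint wording is required, preferably before outcome data by cohort are examined.

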### Complications

All study techniques are in practice today and only surgeons competent in a procedure will be allowed to perform those surgeries. Therefore, there are no anticipated additional risks than would normally be encountered in these patients. All complications will be captured on the electronic complication case report form, including in detail signs and symptoms related with wound infection (tenderness at the wound, swelling around the wound, redness of the wound, heat of the wound). All complications will be graded by the investigator according to the Clavien-Dindo classification [10]. The investigator or designee will monitor the occurrence of complications associated with the surgical procedure, as well as procedure-related and postoperative clinical sequelae; the principal investigator will report complications to the local ethics committee and, if related to the robotic system, to the Initiative EMEIA Complaints Team and to the study sponsor.

### Data collection and management

Data will be collected prospectively according to the schedules outlined in Fig. 2 and Table 1. Enrolled patients will undergo assessments at the following intervals: preoperatively, intraoperatively through to discharge, 30 days, 90 days, 1 and 2 years post-procedure. At baseline and once patient consent has been obtained, patient demographics and medical history (including indication and planned procedure) will be collected. Patient-related quality of life and functional measures will be completed by the patient. Data related to the operative procedure itself will be collected, including procedure timing, personnel, resource utilization, system and instrument use, need for conversion, complications and technical observations. During the perioperative period until discharge, data collected will include wound infection, complications, 30-day mortality, length of stay, and tumor characteristics. During follow-up, patient-related functional outcomes and quality of life measures will be completed and any complications or protocol deviations reported, according the standard follow-up procedure for each center.

**Fig. 2 Fig2:**
[figure not shown]
Study assessments. BMI, body mass index; CME, complete mesocolic excision; CT, computed tomography; ECA, extracorporeal anastomosis; ERAS, enhanced recovery after surgery; EORTC, European Organization for Research and Treatment of Cancer; ICA, intracorporeal anastomosis; PET, positron emission tomography; QLQ-C, quality of life questionnaire for cancer patients; QLQ-CR, quality of life questionnaire for colorectal cancer patients

**Table 1 Tab1:** Assessment schedule

	Baseline	Procedure	Discharge	30 days ±7 days	90 days ±14 days	1 year ±30 days	2 years ±30 days	Unscheduled visit
Informed consent	X							
Demographics and medical history	X							
Procedure details		X						
SIRS (CRP) *Optional: PCT*		X						
Pathology				X				
CT scan/PET scan^c^	X					X	X	
Complications		X^a^	X^a^	X^a^	X^a^	X^a^	X^a^	X^a^
Quality of life: EQOL	X				X	X		
Study exit forms							X^b^	

^a^Complete if applicable; ^b^complete when lost to follow-up, consent withdrawal or subject has completed all study related visits; ^c^CT scan results will be collected if done per the sites standard protocol: every 6 months for malignant disease; after at least 1 year to assess hernia in benign disease. *CRP* C-reactive protein (collected at days 1 and 3 postoperative); *CT* computerized tomography, *PCT* procalcitonin (optional, collected at days 1, 3, 5 postoperative); *PET* positron emission tomography, *SIRS* systemic inflammatory response syndrome

Primary data collection will be performed by a study coordinator or designee. The data will be collected on the electronic case report forms (CRF), hosted in a study-specific, dedicated electronic data collection (EDC) system. The database has been developed and utilized in accordance with international requirements and standards applicable to clinical investigations i.e. good clinical practice (GCP) and is a GCP-compliant environment meeting applicable 21 CFR Part 11 requirements. A copy of the completed CRF will remain on site at the participating center at the end of the study. All data requested on the CRFs will be recorded. All missing data will be explained. The European Society of Coloproctology will conduct two independent snapshot audits during the study, during the first and second years, which will also collect information on all right colectomies performed in the participating institutions.

Study monitoring will be conducted using a risk-based monitoring approach (i.e. most monitoring activities will be performed using remote monitoring functionality by reviewing the data from the EDC system). The on-site monitoring will be conducted on an as-needed basis in situations including, but not limited to, protocol compliance issues, major data discrepancies, and safety issues. In general, the study monitoring functions will be performed by the sponsor or its appointed designee in compliance with recognized GCP, the harmonized standard EN ISO 14155, and local applicable legislation. The major function of the clinical monitor is to observe and assess the quality of the clinical study. It will be the responsibility of the site-appointed research personnel to complete all CRF and to document conformity to the clinical trial protocol throughout the study.

There will be no study-specific tests, either preoperatively or postoperatively, that are beyond what is routine and customary for patients undergoing the surgical procedures under consideration. Patients can choose to withdraw at a time, and the investigator has the right to discontinue patients at their discretion to ensure their wellbeing. In the event of a patient’s early withdrawal from the study, all CRF will be obtained up to the point of withdrawal, with the reason for withdrawal documented, and no further follow-ups will be performed. If a patient cannot be reached during a visit window, a missed visit will be recorded; after three consecutive missed visits, a patient will be considered lost to follow-up and a study exit form will be completed in the electronic CRFs. All protocol deviations will be recorded on the protocol deviation form.

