## Background

The standard surgical treatment for malignant neoplasms of the right colon is right colectomy (hemicolectomy). Open resection is associated with a relatively high rate of complications, but these may be reduced along with blood loss and hospital stay using laparoscopy [1, 2], a minimally-invasive technique in which operations are performed via small incisions (usually 0.5–1.5 cm) at a location distant to the site of interest. There are some limitations to the laparoscopic approach, including loss of a three-dimensional view, poor ergonomics, limited movement dexterity, and tremor [3], which may be overcome with robotic assistance. This minimally-invasive approach offers greater precision, flexibility, and control that minimizes the risk of injury to vessels and nerve structures, and enables oncologic resection [4]. Although longer operative times have been reported with robot right colectomy, the surgery can significantly reduce blood loss, postoperative complications and wound infections, lead to faster recovery of bowel function, fewer conversions to open surgery, and shorter hospital stay compared with laparoscopy [5, 6]. It should be noted that in many studies to date, the operating surgeon was often relatively inexperienced in robot-assisted surgery [5]; operative times can improve significantly with increasing experience [7]. There are also potential advantages in performing intracorporeal anastomosis (ICA, where the anastomosis is performed inside the abdominal cavity during minimally-invasive surgery) compared with extracorporeal anastomosis (ECA, where the anastomosis is performed by pulling out the bowel through a laparotomy). Benefits of ICA include smaller incision length, reduced time to first defecation, reduced short-term morbidity (e.g. less surgical wound infection), decreased rate of incisional hernias and re-interventions, and a shorter hospital stay compared with ECA [8, 9]. It is possible that the ability of the surgeon to perform ICA may be enhanced by robotic assistance, potentially reducing the conversion rate and improving the quality of suturing, but further research is required.

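### Day-3 CRP, part of the secondary SIRS endpoint, is at risk of informative, cohort-dependent missingness under the exclusion rule for missing endpoints

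*Protocol article*

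**What the plan says.** The Outcomes section lists among the secondary endpoints, for all cohorts, "systemic inflammatory response syndrome (C-reactive protein, with optional procalcitonin". The footnote to Table 1 (Data collection and management) fixes the sampling days: "C-reactive protein (collected at days 1 and 3 postoperative", and "procalcitonin (optional, collected at days 1, 3, 5 postoperative". Table 1 ticks SIRS in the Procedure column only.

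The same section sets the assessment times as "preoperatively, intraoperatively through to discharge, 30 days, 90 days, 1 and 2 years post-procedure", which leaves nothing between discharge and day 30. It also states: "There will be no study-specific tests, either preoperatively or postoperatively, that are beyond what is routine and customary".

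On missing data, the Statistical analysis section says "Patients with missing data in any end-point will be excluded from the analyses on that end-point". Multiple imputation is reserved for covariates: "patients with missing data in variables included in the propensity score will have their data imputed using multiple imputation procedures". The three sensitivity analyses that follow apply to the primary endpoints.

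On length of stay, the Background credits ICA with several benefits, ending in "and a shorter hospital stay compared with ECA", and reports shorter stay with robotic surgery than with laparoscopy. It gives no number of days for either. Length of stay is itself a secondary endpoint.

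**The concern.** Discharge happens after the operation and can be influenced by it. Patients who leave before day 3 are plausibly those with a mild inflammatory response, so losing their day-3 CRP is unlikely to be random. If the shares leaving early differ by cohort, a complete-case day-3 comparison sets a more selected group against a less selected one. The cohort with faster recovery keeps relatively more of its inflamed patients, and its mean CRP looks too high. The comparison could then hide a true reduction with ICA or robotic surgery, or suggest an increase where there is none. The planned propensity score does not correct this. It deals with confounding of the choice of technique, not with selection on an event after surgery.

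**Working it through.** The protocol gives no figure for CRP, its missingness or early discharge, so there is nothing to reproduce. The check has two parts.

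**1. Does the stated rule lead to the loss?**

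- Sampling falls on days 1 and 3 (Table 1 footnote).
- No study contact falls between discharge and day 30, and no tests go beyond routine care (Data collection and management). The plan therefore provides no blood draw to recover a day-3 value after discharge.
- A missing endpoint means exclusion from that endpoint's analysis, and outcomes are not imputed (Statistical analysis).

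A patient discharged on day 2 would normally have a day-1 CRP but no day-3 CRP, and would drop out of any day-3 comparison. The Background gives the likely direction: shorter stay with ICA and with robotic surgery.

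**2. How large could the bias be?**

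From the protocol: 300 patients per cohort (Patient recruitment). Assumed, because the protocol gives neither: the share q discharged before day 3, and the correlation ρ between log CRP on day 3 and length of stay, taken as 0.2 to 0.5. True day-3 CRP is taken as equal in both cohorts, and CRP and stay as bivariate normal on suitable scales.

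If the fraction q with the shortest stay is removed, the mean log CRP of those who remain rises, in SD units, by

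shift(q) = ρ × φ(z_q) / (1 − q),

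where z_q is the normal quantile of q and φ the normal density. The multiplier of ρ is:

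- q = 5%: 0.1031 / 0.95 = 0.109
- q = 10%: 0.1755 / 0.90 = 0.195
- q = 20%: 0.2800 / 0.80 = 0.350
- q = 30%: 0.3477 / 0.70 = 0.497

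The bias is ρ times the difference between the two cohorts' multipliers:

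| Discharged before day 3 (longer-stay v shorter-stay cohort) | Kept of 300 | Difference in multipliers | Bias, ρ = 0.2 to 0.5 |
|---|---|---|---|
| 5% v 5% | 285 v 285 | 0 | 0 SD |
| 5% v 10% | 285 v 270 | 0.086 | 0.02–0.04 SD |
| 10% v 20% | 270 v 240 | 0.155 | 0.03–0.08 SD |
| 10% v 30% | 270 v 210 | 0.302 | 0.06–0.15 SD |

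For scale, the standard error of a simple difference in means, in SD units, is √(1/n₁ + 1/n₂). With 10% v 30% it is √(1/270 + 1/210) = 0.092, so the bias is 0.060/0.092 = 0.7 to 0.151/0.092 = 1.6 standard errors. The false-positive rate of a two-sided 5% test becomes about 10% to 37%. With 5% v 10% the standard error is √(1/285 + 1/270) = 0.085, the bias is 0.2 to 0.5 standard errors, and the false-positive rate is about 5% to 8%. These figures ignore covariate adjustment and clustering by hospital.

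**The case against.** The strongest reply is that the endpoint is SIRS, not day-3 CRP. The article does not say how SIRS is derived from CRP, whether both days are needed, or what happens when only day 1 is available. Its list of models for secondary endpoints does not mention SIRS, and it refers the analyses to a statistical analysis plan that is not shown. That stands in part. A reader might infer that patients discharged early cannot be scored for SIRS at all; the text does not support this, since they would still have a day-1 value. The missing scoring rule is not itself the finding. What the article does fix is exclusion for any missing endpoint, with imputation confined to propensity-score variables. An analysis plan that follows this inherits the problem for any day-3 comparison.

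A reader might also infer that the day-3 sample must be taken in hospital. No place of sampling is stated, and limiting tests to routine care could equally mean that the day-3 CRP is regarded as routine. The absence of any contact before day 30 makes an inpatient sample the likely case, not a certain one.

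A third tempting reading is that the loss falls mostly on the ICA and robotic cohorts. The documents show only that a shorter average stay is expected. They give no stay distribution, and a shorter average does not establish different shares leaving before day 3. If centre discharge policy drives early discharge, for instance through enhanced-recovery protocols that are desirable but not required, the patient-level link with CRP is weaker and the bias smaller.

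Finally, the protocol requires missing data to be explained, so early discharge should be visible as a reason. That helps with reporting but does not alter the comparison.

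**Conclusion.** The concern holds as a risk created by a stated rule. The likely direction is against the cohorts with shorter stay. The size runs from nothing, if equal shares leave early, to a modest 0.06–0.15 SD with 10% v 30%, and the documents cannot place it within that range. The conclusion rests on three assumptions: that day-3 samples are in practice taken before discharge, that early discharge goes with lower CRP, and that the shares leaving early differ by cohort as the Background suggests. One secondary endpoint is affected; the primary composite is not. The change is worth making because it is cheap and best settled before results are seen.

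**What to change.** Exempt the SIRS/CRP endpoint from the complete-case exclusion. Analyse log CRP at days 1 and 3 in one repeated-measures (mixed) model with cohort, day and their interaction, so that patients discharged before day 3 contribute their day-1 value. Report by cohort the share discharged before day 3, and before day 5 for the optional procalcitonin.

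This changes analysis wording only and needs no new samples or visits. The cost is an assumption that missingness depends on observed values such as day-1 CRP. Selection that day-1 CRP does not capture would remain, which is why the discharge shares should be shown beside the result.

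Making day 1 the lead comparison, or ranking early discharges as the best outcome, is optional. The first says less about later inflammation, and the second builds length of stay, already a separate endpoint, into the CRP result.
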